### (iii) Interventions

The Intervention Group--The eight-week Physical-Psychological Integrative online-group intervention

Part I: Physical exercise. A guiding video of performing exercises was specifically developed for the SCI population by two experienced physiotherapists in Hong Kong. The video mainly includes warm-up, mobilization, strength exercises, aerobic exercises, and cool-down sessions.

Part II: An eight-week online intervention. The PPI intervention includes eight weekly online groups (with 4-5 participants in a group) sessions (with each session lasting for 60-90 minutes). At the beginning of each online group meeting, the intervention provider will use motivational interviewing techniques [23] to promote participants' adherence to the physical activity program mentioned in Part I, followed by online group psychological intervention. The content of the intervention will be adapted from the mindfulness-based stress reduction proposed by Kabat Zinn (1992), practice guideline of 'mindfulness for health' to relieve pain, reduce stress, and restore well-being [24]. The content of the intervention includes eight themes/sessions (the details of the intervention content are shown in Appendix 2): Session 1- Orientation and engagement; Session 2- Awareness and Acceptance; Session 3- Non-judgement; Session 4- Stay present and let go; Session 5- Our thoughts are not real & Response without reacting; Session 6- Empowerment of self-management and discuss pain management; Session 7- Seek out pleasant things and social support; Session 8- Review the intervention and end the programme. Two audio-tape recorded sessions (i.e., 20 minutes each) of mindfulness practice will be given to the participants for their daily practice. The intervention will be carried out by an experienced social worker trained in psychology, motivational interviewing, and mindfulness-based stress reduction.

### The control group

Participants in the control group will receive a video call (approximately 60 minutes each week for eight weeks) from the trained research assistant with psychological background, i.e., to provide general physical and psychological suggestions (e.g., encouragement of performing physical activities, and communication skills with family members/friends, and engagement in the community life). This is to control the contact effects of the PPI intervention.

### Study attrition and data fidelity

The research assistant will contact the participants via phone/WhatsApp and encourage them to attend the online meetings as scheduled. Fitbit wristband activity trackers will be used as incentives for the participants to remain in the study. The group intervention attendance and dropout of participants will be monitored by the intervention facilitator, and a logbook will be used to record their attendance. Intervention sessions will be audio-taped with participants' consent for reviews and discussion of improvements among the research team. A researcher independent of the study execution will be responsible for periodic monitoring of data collection progress, quality, and safety. All adverse events will be identified, reported, and handled cautiously.

### Ethical considerations

Ethical approval will be obtained from the Hong Kong Polytechnic University. This study will be performed in accordance with the Helsinki Declaration. Written informed consent will be obtained from all participants before the baseline assessments of the study, and will also be obtained from purposely sampled participants prior to all focus-group interviews. Participation is entirely voluntary for people with SCI and they can withdraw from the research at any time without any penalty. Participants' identities and data (information

collected and videotape records) will be protected by maintaining anonymity and confidentiality. Only authorized personnel can access the data for analysis.

(iv) Data processing and analysis

Feasibility and acceptability

**The feasibility** assessment of subject recruitment and follow-up will include (1) time taken to recruit the target sample size; (2) recruitment rate: the number of eligible participants approached who agree to consent divided by all subjects eligible to participate; (3) retention rate: the number of participants who complete the study divided by all participants who agree to consent; (4) drop-out rate: the number of participants who dropped out after randomization divided by all participants who agree to consent; and (5) reasons for dropping out will be collected from participants who dropped out.

**The acceptability** of the intervention will be indicated by (1) adherence rate: the number of PPI intervention sessions practiced divided by the total number of required sessions; (2) adverse events record associated with PPI intervention; and (3) satisfaction: participants' satisfaction with the intervention will be assessed with the Client Satisfaction Questionnaire [25]. The acceptability of the intervention will also be assessed by focus-group interviews with a purposive sample of participants who completed the whole intervention sessions and those who withdrew from the intervention period. Participants' perspectives about the acceptability, strengths, and limitations of the study and suggestions on the improvements of the interventions will be explored.

Preliminary effectiveness

All participants will be assessed at pre-, post-intervention, and 3-month follow-up by the research assistant. A self-designed form will be used to collect data on participants' socio-demographics and medical history, including age, gender,

employment, marital status, ethnicity, cause, level of injury, and time since the injury. The following outcomes/instruments will be used to assess the preliminary effects of the PPI intervention. Effect sizes (e.g., Cohen's d) and confidential intervals will be calculated to estimate the sample size for a future fully powered randomized controlled trial.

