#### Sample size

As this proposed study is to develop and evaluate the feasibility, acceptability, and preliminary effectiveness of the PPI intervention, a widely acceptable sample size (i.e., 30 participants in each study group) for a preliminary analysis to examine intervention feasibility and to estimate a between-group effect will be adopted [22]. Considering a 20% attrition rate, 36 people with SCI per study group (i.e., 72 people in total) will be recruited. A purposive sampling by key informants (containing both participants who completed the whole intervention sessions and those who withdrew from the intervention period) will be conducted for focus-group interviews (i.e., 4-5 participants per group), until saturation of the information was reached.

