#### Randomization and masking

After the completion of the baseline assessment, eligible participants will be randomly allocated to two study groups. The random allocation will be conducted by an independent researcher with an external randomization service (i.e., sealedenvelope.com), using random permuted block sizes (i.e., 4 or 6) to ensure balanced group numbers. Participants will not be blinded due to the nature of the intervention. Participants will be reminded to keep the intervention content confidential and not discuss this with participants in the control group to avoid contamination. Assessor-blind is not adopted as measurements are self-reported. Assistance provided by caregivers and research assistants might be needed for those who have difficulties in filling out surveys.

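### The drop-out rate counts losses after randomisation but divides by everyone who consented, so it is understated whenever a consenter is not randomised

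*Protocol*

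**What the plan says.** Protocol section (iv), under Feasibility and acceptability, lists five feasibility measures. Three of them matter here:

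- The recruitment rate is "the number of eligible participants approached who agree to consent divided by all subjects eligible to participate".
- The third measure is the "retention rate: the number of participants who complete the study divided by all participants who agree to consent".
- The fourth is the "drop-out rate: the number of participants who dropped out after randomization divided by all participants who agree to consent".

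The order of events is fixed in two other places. Ethical considerations states: "Written informed consent will be obtained from all participants before the baseline assessments of the study". Randomization and masking states: "After the completion of the baseline assessment, eligible participants will be randomly allocated to two study groups".

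The attrition allowance is in the Sample size section: "Considering a 20% attrition rate, 36 people with SCI per study group (i.e., 72 people in total) will be recruited".

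The protocol defines no retention or drop-out rate over randomised participants, and gives no expected loss between consent and randomisation.

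**The concern.** The drop-out rate takes its numerator and its denominator from two different populations. The numerator can contain only people who were allocated. The denominator is everyone who consented, a group formed before baseline and therefore before allocation. A person who consents and withdraws before allocation is in the second group and cannot be in the first. Each such person lowers the reported drop-out rate without any change in what happened after randomisation.

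Feasibility is the first aim the protocol names, and retention and drop-out are two of its five feasibility measures. The pilot is meant to prepare a fully powered trial, and for that purpose an understated drop-out rate is the unhelpful direction of error. The natural yardstick in the document, the 20% allowance, is applied to each study group, which is a randomised population. Neither rate as defined is on that scale.

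**Working it through.** **The plan's own figure.** The Sample size section goes from 30 to 36 per group at 20% attrition. This is reproduced by 30 × 1.20 = 36, and 2 × 36 = 72. The allowance is therefore a loss from people in a study group. (Whether multiplying by 1.20 is the right way to allow for 20% loss is a separate question and is not needed here.)

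**Notation.** R = randomised, C = consented, L = lost after randomisation, and completers = R − L.

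- Drop-out among the randomised: L/R. Protocol formula: L/C = (L/R) × (R/C).
- Retention among the randomised: (R − L)/R. Protocol formula: (R − L)/C = [(R − L)/R] × (R/C).
- Sum of the two protocol rates: R/C, which is 100% only if C = R.

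Both rates shrink by the same factor. Read as post-randomisation measures, drop-out then looks better than it was and retention looks worse.

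**Numbers.** R = 72 is the protocol's target. L = 14 is assumed, chosen because it is close to 20% of 72 (14.4). C is assumed and varied, because the protocol gives no value.

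| Consented C | Not randomised, (C − 72)/C | Drop-out, 14/C | Retention, 58/C | Sum, 72/C |
|---|---|---|---|---|
| 72 | 0% | 19.4% | 80.6% | 100% |
| 76 | 5.3% | 18.4% | 76.3% | 94.7% |
| 80 | 10.0% | 17.5% | 72.5% | 90.0% |
| 90 | 20.0% | 15.6% | 64.4% | 80.0% |

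The first row is also the result with a randomised denominator, whatever C is.

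**In reverse.** A reported drop-out rate of exactly 20% corresponds to a post-randomisation rate of 20% × C/72: 21.1% at C = 76, 22.2% at C = 80 and 25.0% at C = 90.

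**The case against.** The strongest reply is that this may be a wording defect with little effect. Several parts of it stand.

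- *The bias is conditional.* The formula goes wrong only if some consenters are not allocated. A reader might infer that the two rates will be wrong; the documents do not support that, because they give no figure for this loss and it could be zero.
- *Eligibility seems to be settled largely before consent.* The recruitment rate counts consenters from among eligible people approached. A reader might picture many people consenting and then failing a screen, but the reference to eligible participants at allocation does not establish a second screen. What remains is withdrawal between consent and the end of baseline. The protocol lets participants withdraw at any time, so this is possible but may be rare.
- *Retention over consented is a coherent quantity.* It measures yield from consent to completion, and nothing in the protocol requires it to add to 100% with drop-out. It is a different measure from post-randomisation retention, not an arithmetic error.
- *Differential drop-out remains visible.* A reader might infer that it cannot be seen, since people never randomised have no arm. But every post-randomisation loss has a known arm, numbers randomised per arm are known, attendance and drop-out are monitored, and reasons for dropping out are collected. A flow chart following CONSORT is also named; it is not visible in the copy reviewed, so it cannot be assumed to lack counts by arm.
- *The rates are not stated inputs to the next trial's sample size.* That too might be inferred, but section (iv) names effect sizes and confidence intervals for the purpose. No progression threshold is attached to either rate.
- *Sampling error is larger than the shift in drop-out.* The 95% Wilson interval for 14/72 is about 12% to 30%, and even the case of 90 consenters moves the estimate by only 19.4 − 15.6 = 3.8 percentage points.

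None of this repairs the drop-out definition. Its numerator and denominator still come from different populations, the protocol itself fixes the formula, and no other section corrects it. Sampling error does not excuse a bias of known direction that can be removed by changing one word.

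**Conclusion.** The drop-out rate is wrong as defined. It understates post-randomisation drop-out by the factor randomised/consented whenever consented exceeds randomised. In the assumed illustration (72 randomised, 14 lost), 19.4% reads as 18.4%, 17.5% or 15.6% with 76, 80 or 90 consented. The direction is certain; the size depends on a loss the protocol does not state, and is nil if everyone who consents is randomised.

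The retention rate is valid as an overall yield, but it should not be read as post-randomisation retention, as the complement of drop-out, or as a check on the 20% allowance. That check can still be made from the counts of participants randomised and completing.

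This is a modest correction to a feasibility definition. It affects no between-group comparison of outcomes, and correct rates can be calculated later from the same counts. It is still worth settling before results are known, because feasibility is a named aim and the rule as written gives a misleading figure if followed.

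**What to change.** In section (iv), under Feasibility and acceptability:

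1. Define drop-out as randomised participants lost, divided by participants randomised.
2. Define retention as randomised participants completing the study, divided by participants randomised.
3. Report both overall and by arm.
4. Report loss before allocation on its own line, as (consented − randomised)/consented.
5. If completers over consented is still wanted, keep it under a separate label such as overall yield from consent to completion.

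The cost is two reworded definitions and one added line. All the counts will already be held, so no new data, visits or participants are needed.

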This study **aims** to evaluate the feasibility, acceptability, and preliminary effects of an eight-week Physical-Psychological Integrative (PPI) online-group intervention on physical inactivity, depression, and chronic pain for people with SCI living in the community.

Research hypotheses: when compared with those the control group (online telephone didactic education), participants in the PPI intervention group will indicate significantly greater:

1. Improvements in *the minutes of performing the moderate-to-rigorous physical activity as well as the number of days they are physically active* for a total of at least 60 minutes or more per day at post-intervention, and 3-month follow-up;
2. Improvements *in depression and chronic pain* at post-intervention, and 3-month follow-up;
3. Improvements in *mindfulness skills and quality of life* at post-intervention, and 3-month follow-up.

c) Plan of investigation:

(i) Study method/design

An open-label, two-arm pilot RCT will be conducted to investigate the effects between the intervention (PPI online-group intervention) and the control group (brief online didactic education) for people with SCI living in the community over a 3-month follow-up. Qualitative interviews with focus groups involving participants in the PPI intervention group will be conducted post-intervention,

to explore participants' views about acceptance, strengths and limitations, and suggested improvements of the intervention. Participants' recruitment and other study procedures are summarized in a flow chart (Appendix 1) according to the CONSORT statement.

(ii) Participants (subjects)

Study participants will be recruited from the Hong Kong Direction Association for the Handicapped and other community centers in Hong Kong, where groups of people with physical impairments can be reached. The Hong Kong Direction Association for the Handicapped (<https://www.4limb.org/>) is a **typical non-government organization that serves a large group of people with severe physical impairment/handicaps in Hong Kong**. According to personal communication with the President of the Association, there are approximately a thousand members of the association and over 30% of them are SCI survivors. Emails/phone call invitations will be sent to potential participants and advertising posters will also be used to encourage them to participate.

Eligibility:

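### The only adverse-event outcome the protocol names is limited to PPI-associated events, so it lacks the background rate that the control arm could supply

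*Protocol*

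**What the plan says.** Under Feasibility and acceptability, in section (iv) of the protocol, the acceptability "of the intervention will be indicated by (1) adherence rate" and two further items. Item (2) is the "adverse events record associated with PPI intervention"; item (3) is satisfaction. The Data analysis section names no adverse-event measure, so item (2) is the only one among the outcomes and analyses.

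Study attrition and data fidelity is wider: "All adverse events will be identified, reported, and handled cautiously". That sentence is limited neither by arm nor by relatedness. The same section adds that "A researcher independent of the study execution will be responsible for periodic monitoring of data collection progress, quality, and safety".

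Three other statements bear on the point:

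- Study method/design: "An open-label, two-arm pilot RCT will be conducted".
- Randomization and masking: "Participants will not be blinded due to the nature of the intervention", and "Assessor-blind is not adopted as measurements are self-reported".
- The control group: the weekly video calls over eight weeks include "encouragement of performing physical activities".

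**The concern.** Item (2) is narrower than the ascertainment promised elsewhere in the protocol, and the part it drops is the part that makes a harm count interpretable. This population has a heavy background of pain and low mood. Participants are relatively inactive at entry, because those active for more than 150 minutes a week are excluded, and the PPI arm then follows a programme with strength and aerobic exercise. Complaints will arise that could come from the injury or from the exercise, and these are hard to tell apart case by case. A randomised control arm shows how often such complaints occur without PPI. Control participants are themselves encouraged to be active and have regular contact with staff, so their events both can occur and can be recorded.

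The pilot is meant to lay the foundation for a fully powered trial. Harm information that cannot be set against a background rate is of limited use for that decision.

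**Working it through.** The protocol states no adverse-event rate, threshold or power, so there is no figure of its own to reproduce. The check is mainly of wording, with some arithmetic for scale.

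**Step 1. The two readings of item (2).**

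| Reading of associated | PPI-arm event | Control-arm event |
|---|---|---|
| Causally related to PPI | Counts only if judged related | Cannot count |
| Occurring in the PPI arm | Counts | Cannot count |

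The missing comparator follows from both readings. Dependence on attribution follows only from the first. On that reading the protocol names neither an assessor nor criteria, and the trial is open-label.

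**Step 2. Is the wider sentence contradicted?** Collecting and reporting every event is compatible with using a subset of events as one indicator. The two sections differ in scope but do not conflict.

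**Step 3. Background burden.** Inputs are 36 per arm (Sample size), chronic pain in around 70% to 80%, and depression in 9.8% to 63.9% (Introduction).

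- Pain: 36 × 0.70 = 25.2 and 36 × 0.80 = 28.8, about 25 to 29 participants per arm.
- Depression: 36 × 0.098 = 3.5 and 36 × 0.639 = 23.0, about 4 to 23 per arm.

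These are prevalences, not event rates. They show only that such complaints are to be expected without any intervention.

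**Step 4. What item (2) could report.** Assume that 20% of participants per arm have an event: 36 × 0.20 = 7.2.

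- Causal reading: the PPI count depends on the share judged related. A share of 25% gives 7.2 × 0.25 = 1.8, 50% gives 3.6, and 100% gives 7.2. The full range is 0 to about 7.
- Arm reading: about 7 of 36 are reported. Without a control figure, this fits both no excess (control also 20%) and a doubling (control 10%, or 3.6 participants).

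**Step 5. What a comparison by arm would give.** The 95% half-width is 1.96 × √[p₁(1−p₁)/36 + p₀(1−p₀)/36]. All rates are assumed.

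| PPI rate | Control rate | Half-width (percentage points) |
|---|---|---|
| 10% | 10% | 13.9 |
| 20% | 20% | 18.5 |
| 40% | 20% | 20.7 |

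For 20% in both arms: √(2 × 0.2 × 0.8 / 36) = 0.0943, and 1.96 × 0.0943 = 0.185. Power at the 5% two-sided level is about 22% for 20% against 10%, and about 46% for 40% against 20%. The comparison can describe but not test.

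**The case against.** The strongest reply is that item (2) measures the acceptability of PPI, not safety. It sits beside adherence to PPI sessions, which is also specific to PPI. Safety is provided for separately, through the reporting of all events and periodic monitoring by an independent researcher. This stands, and it rules out two stronger readings. A reader might infer that the protocol contradicts itself, but Step 2 shows that it does not. A reader might also take item (2) for the trial's safety result, or conclude that control-arm events go unreported. The protocol says neither.

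A second reply is that unblinded staff are nowhere said to decide relatedness. That is correct. The masking section concerns participants and self-reported outcomes, and attribution matters only on the causal reading.

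Third, pain intensity and the PHQ-9 are primary outcomes, measured in all participants and compared between arms by generalised estimating equations. So pain and mood are not without a randomised comparison. This reduces the gap but does not close it: mean scores do not replace event counts, and musculoskeletal complaints are not covered.

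Fourth, tabulating adverse events by arm is ordinary content for a statistical analysis plan, and that plan is not shown. The absence of such a table is indeed no finding. The point here is a definition that the protocol itself states, and states narrowly. An analysis plan that followed it faithfully would carry the restriction forward.

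Finally, a comparison by arm would not be free of bias. The trial is open-label, and contact differs: groups of 4 to 5 led by a social worker against calls from a research assistant. Reporting may differ accordingly. This stands and shapes the fix.

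**Conclusion.** The point holds as a cheap improvement, not as a demonstrated error. The only named adverse-event outcome has no control-arm counterpart on either reading of its undefined term, and on the causal reading it also depends on attribution without stated criteria. The wording alone supports this; no assumed rate is needed.

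The size is illustrative, because the documents give no event rate. At an assumed 20% per arm, about 7 control participants with an event would be missing from the indicator, and on the causal reading the PPI figure could be anything from 0 to about 7. Adding the control arm would supply the missing background rate but would not settle whether PPI causes harm: the interval is about ±14 to ±21 percentage points over the assumed rates shown.

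**What to change.** Reword item (2) as the number and proportion of participants in each arm with any adverse event, and with any serious adverse event, from randomisation to the 3-month follow-up, regardless of relationship. Record relatedness to the allocated intervention as a separate field, and state who judges it and by what criteria.

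Ask about events with the same question at the same times in both arms. The post-intervention and 3-month assessments, already planned for all participants, serve this purpose. The control calls do not, because they end at eight weeks and differ in format from the PPI groups. Report the two arms side by side with confidence intervals, as description and without a test.

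The cost is one reworded definition, one question added to two existing assessments, and one table. It uses events that the protocol already undertakes to identify, and it changes no treatment. The downsides are a longer list of non-specific events, some reliance on recall between assessments, wide intervals, and reporting that may still differ between arms because allocation is known. The report should state that last limitation.
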